### Interventions

The interventions will start the same day as the baseline examination or the day after and will be performed on all weekdays until discharge. Intervention 1 is adapted from the exercise programme by Ortiz-Alonso *et al*,^11^ and intervention 2 is adapted from the exercise programme by Martinez-Velilla *et al*.^10^ The interventions will be offered in addition to usual care.

#### Intervention 1 (simple exercise programme)

This intervention will include up to four sessions per day (total duration 20–30 min/day). It consists of sit-to stand exercises and walking along the corridor of the ward (for those who can walk). The exercises will mainly be led by physiotherapists, and, when suitable, intervention 1 will be performed in connection with regular routines in the usual care (table 1). At discharge, the participants will be encouraged to continue with the exercise programme at home, 3 days per week during 6 weeks. In addition to oral instructions, they will receive written instructions with pictures on how to perform the exercise.^11^

**Table 1 T1:** Overview of the interventions

Intervention	Timing/frequency and duration of exercises	Description	Dose
Intervention 1 (Simple exercise programme)	Up to four times/day (total duration 20–30 min/day)	Sit-to-stand exercises. Rising from a chair and sitting down again repeatedly, using armrest and assistance if needed.	1–3 sets of up to 10 repetitions, depending on the participant’s ability.
		Walking. Walking along the corridor, using walking aid and assistance if needed.	3–10 min per session, with resting periods if needed.
Intervention 2 (Comprehensive exercise programme)	Before lunch (duration 20 min)	Strengthening exercises Sit-to-stand exercises. Rising from a chair and sitting down again repeatedly, using armrest and assistance if needed. Knee extensions. Knee extensions in a sitting position, with a weight cuff on the ancle. Repeat with both legs. Standing push-ups. Bending and stretching arms leaning on a wall.	1–3 sets of up to 10 repetitions, depending on the participant’s ability.
		Balance exercises Semi-tandem stance. One foot placed in front of the other foot, with the big toe of the back foot in the groove of the front foot. Repeat on the other side. Line walking. Walking in a straight line, placing one foot in front of the other and vice versa. Walking with small obstacles. Walking around small obstacles and/or stepping over small obstacles. Stepping practice. Stepping up and down on a step board or staircase. Weight transfer. Standing up, transferring the weight from one leg to the other. Proprioceptive exercises. Walking on an unstable surface.	Dose adapted to the participant’s ability and time frame.
	Afternoon (duration 20 min)	Knee extensions. Knee extensions in a sitting position. Repeat with both legs. Knee flexion. Standing knee flexions, holding on to a chair. Repeat with both legs. Hip abduction. Standing hip abduction with the participant standing, holding on to a chair. Repeat with both legs. Hand exercise with handgrip ball. Walking. Walking along the corridor, using walking aid and assistance if needed.	1–3 sets of up to 10 repetitions for, depending on the participant’s ability.

#### Intervention 2 (comprehensive exercise programme)

This intervention consists of two daily sessions (morning and afternoon) with a duration of 20 min each. The morning session includes individualised supervised progressive resistance, balance and walking exercise, tailored to each participant’s capacity. The resistance exercise includes using weight cuffs, which mainly involves lower-extremity muscles. Balance and gait exercises include different exercises such as line walking, stepping practice and walking with small obstacles. The evening session consists of functional exercises using light loads, such as knee extension and flexion, hand exercise with a ball, and daily walking exercise (for those who can walk).^10^ The exercises will be led by physiotherapists (table 1).

#### Control group

The control group will receive usual care. Usual care is based on teamwork, which includes physiotherapy. The physiotherapy focuses on mobility assessments, and the patients may receive a limited amount of functional training when needed. However, we expect that the participants often have a limited amount of physical activity during the hospital stay.^14^

Daily logbooks will be used during the hospital stay to register the number of attended exercise sessions for the intervention groups, as well as treatment safety for all groups (by registering adverse events during the hospital stay, eg, falls). Furthermore, exercise diaries will be used during 6 weeks to register the self-training conducted at home in intervention 1.

#### Data collection

Physical function, ADL, HRQL, sarcopenia and falls will be assessed at baseline (hospital admission), discharge and 3 months after discharge. Research staff blinded to group allocation will conduct the tests and administer the questionnaires at the hospital (for the baseline and discharge evaluations) and at the home of the participants (for the 3-month evaluation). The 6-month and the 1-year evaluation will be conducted using patient records (for hospital readmissions and mortality) (table 2).

**Table 2 T2:** Time of assessment of the different variables in the trial

	Time point				
Assessment	Baseline (hospital admission)	After exercise/control period (discharge)	3 months after discharge	6 months after discharge	1 year after discharge
Primary outcome					
Physical function	X	X	X		
Secondary outcomes					
Activities of daily living	X	X	X		
Health-related quality of life	X	X	X		
Sarcopenia	X	X	X		
Falls after inclusion		X	X		
Hospital readmissions			X	X	X
Mortality			X	X	X
Additional data					
Frailty status	X				
Nutritional risk	X				
Nutritional supplementation	Continuously collected during the hospitalisation				
Falls in the previous year	X				
Demographic data	X				
Reason for hospital admission	X				
Comorbidities	X				
Length of hospital stay		X			
Discharge destination		X			

The primary outcome will be lower extremity physical function, assessed according to the Short Physical Performance Battery (SPPB).^15^ The SPPB has three components: standing balance, walking speed and the chair stand test for lower extremity strength. It has been validated in older adults living with frailty, is sensitive to change, and predicts a wide range of clinical outcomes.^16 17^

Secondary outcomes will be ADL (according to the Barthel Index),^18^ HRQL (according to the EuroQol-5 Dimension),^19^ presence of sarcopenia (defined by handgrip strength, calf circumference and arm circumference), according to the European Working Group’s revised criteria on Sarcopenia in Older People,^20^ and number of falls during follow-up (according to the logbooks at the hospital, and self-report at the 3-month follow-up). Data on vital status and number of readmissions up to 1 year after discharge will be collected using patient records.

Baseline data will also be collected from patient records including demographic data (age, sex and cohabitation status), reason for hospital admission, comorbidities, frailty status and nutritional risk. Disease diagnoses (reason for hospital admission and comorbidities) will be coded based on the International Classification of Diseases 10th Revision, and further operationalised using a previously described methodology.^21^ Frailty status will be defined according to the Clinical Frailty Scale,^22^ and nutritional risk will be defined according to the Mini Nutritional Assessment-Short Form.^23^ Type and amount of nutritional supplementation consumed during the hospitalisation (if applicable) will be recorded in a logbook. Falls in the previous year will be assessed according to self-report at baseline. Length of hospital stay and discharge destination will be registered at discharge.

#### Data analysis

##### Power of the trial

We estimate that 264 participants should be included in the main RCT to enable detection of a clinically meaningful difference of one point in the main outcome (SPPB) at 3 months after discharge,^24^ when power is 0.80 and alpha is 0.05 (three group comparison). To take into account, approximately 20%of deaths or dropouts during 3 months, 320 participants should be included in the trial.

We will use the intention-to-treat approach. Between-group comparisons of change in the continuous variables from baseline to follow-up will be conducted using linear mixed effects models, with adjustments for baseline scores. To account for deaths and lost to follow-up, we will model the group comparisons through joint models, which will be performed by simultaneously estimating both a linear mixed model and a Cox’s proportional hazard regression model. Group differences in the number of readmissions will be examined using ordinal logistic regression models. Binary logistic regression models will be employed to examine between group differences in binary outcomes, and Cox’s proportional hazard regression model will be used for mortality data. Multiplicative interactions between sex and group allocation in relation to the outcomes will also be examined. Statistical analyses will be performed with Stata and R (version 16).

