## Methods and analysis

### Trial design

The PREV_FUNC study will be conducted in accordance with the Consolidated Standards of Reporting Trials.^12^ It is a three-armed single blind block randomised controlled multi-centre trial. Participants will be included consecutively from geriatric medical departments at four hospitals in Stockholm, Sweden. A flow chart of the participants is shown in figure 1. The patients will be included in the control group or one of the intervention groups in a time-dependent manner: participants will be recruited to each group during blocks of 2–3 weeks, which will be repeated until the end of the trial. The order of the groups will be randomised for each trial site (randomisation will be done by the responsible researchers). The block design has been chosen to avoid copresence of participants from intervention and control groups at the same department; that is, to prevent the exercises in the intervention groups from spreading to usual treatment and risk contaminating the control group.^11 12^ Eligible subjects will be invited to participate in the trial within 36 hours of admission and the baseline examination will be conducted directly after the inclusion. The trial has been registered at ClinicalTrials.gov, NCT05366075. This protocol is reported in accordance with the Standard Protocol Items: Recommendations for Interventional Trials.^13^

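### Arms are allocated by 2–3 week calendar block within hospital, but the stated 0.80 power describes no allowance for within-block correlation and no listed model names a site or block term

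*Protocol article*

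**What the plan says.** Trial design: patients enter an arm according to when they are admitted. "participants will be recruited to each group during blocks of 2–3 weeks, which will be repeated until the end of the trial". The random element is one level up: "The order of the groups will be randomised for each trial site". The stated reason is to keep intervention and control participants from being on the same department together. The Discussion acknowledges that this is not a classic randomisation, but treats only selection bias and contamination as consequences. Correlation within a block is not mentioned.

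Under its power heading, the article states: "We estimate that 264 participants should be included in the main RCT to enable detection of a clinically meaningful difference of one point" on the SPPB at 3 months, "when power is 0.80 and alpha is 0.05 (three group comparison"). The only inflation described is for "approximately 20%of deaths or dropouts during 3 months, 320 participants should be included in the trial". No standard deviation, intraclass correlation, block size, number of blocks or design effect is given.

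The analysis text under the same heading plans "linear mixed effects models, with adjustments for baseline scores" for continuous outcomes, and joint models that combine the mixed model with a Cox model. Readmissions get ordinal logistic regression, binary outcomes binary logistic regression, and mortality Cox regression. The only covariate adjustment named is the baseline score, and the only interaction is sex by group.

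**The concern.** The unit that receives an arm is the hospital-by-period block, not the patient. All participants recruited at one hospital in one block are in the same arm, so the treatment contrast varies only between blocks. If outcomes within a block are more alike than outcomes in different blocks of the same hospital, for example through season, staffing or recruitment behaviour, then a model that treats participants as independent understates the standard error of that contrast. Intervals come out too narrow, the 5% test rejects too often, and a test that handles the blocks correctly has less than the stated power.

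This is not only a matter of analysis detail left to a later plan. The unqualified 0.80 and the allocation scheme that qualifies it both stand in this article, and the basis of the sample size belongs in the protocol.

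**Working it through.** **1. The plan's own figure.** The article gives a difference of 1 point, power 0.80, alpha 0.05 and 264 participants. Assumed here: equal allocation (264/3 = 88 per arm), two-sided testing, and an unadjusted two-sample comparison at 0.05 per pair. No SD is given, so 264 cannot be reproduced independently; one can only solve for the SD that yields it.

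- Normal approximation: n per arm = 2·SD²·(1.960 + 0.842)²/1², so SD = √(88/2)/2.802 = 2.37.
- Two-sample t-test with 88 per arm and 80% power: SD = 2.35.
- Other readings of the three-group comparison: 2.15 with alpha 0.05/2, 2.05 with 0.05/3, and 2.12 or 2.45 for a three-group F test, depending on the pattern of means.

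The figure is therefore compatible with ordinary individual-randomisation formulas and SDs of about 2.05–2.45. The rest uses 2.35.

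**2. Number and size of blocks.** Recruitment from September 2022 to December 2023 (Trial status) is at most 122 + 365 = 487 days, or 69.6 weeks. With four hospitals:

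- 2-week blocks: 4 × 69.6/2 = 139 blocks; 264/139 = 1.90 evaluable per block.
- 3-week blocks: 4 × 69.6/3 = 93 blocks; 264/93 = about 2.8 (2.85 before rounding the block count).

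**3. Effect of clustering.** The design effect is DE = 1 + (m − 1)·ICC, where m is the evaluable number per block. The ICC is an assumption; the article gives none. Type I error of a test that ignores blocks = 2·[1 − Φ(1.96/√DE)]. Power is that of the t-test with 88/DE per arm, difference 1 and SD 2.35.

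| m | ICC | DE | Effective n per arm | Type I error | Power |
|---|---|---|---|---|---|
| 1.90 | 0.02 | 1.02 | 86.4 | 5.2% | 79.3% |
| 1.90 | 0.05 | 1.04 | 84.2 | 5.5% | 78.2% |
| 1.90 | 0.10 | 1.09 | 80.8 | 6.0% | 76.5% |
| 2.85 | 0.02 | 1.04 | 84.9 | 5.4% | 78.5% |
| 2.85 | 0.05 | 1.09 | 80.6 | 6.1% | 76.4% |
| 2.85 | 0.10 | 1.18 | 74.3 | 7.2% | 73.0% |

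**4. Sensitivity to the schedule.** If recruitment is concentrated in fewer blocks of 8–10 evaluable participants (264/8 = 33 to 264/10 = about 26 blocks), an ICC of 0.05 gives DE = 1.35–1.45, power of about 67%–64% and type I error of about 9%–10%. Uneven block sizes also raise DE, because m is replaced by (1 + CV²)·m. The article gives no basis for choosing a CV, so no single figure is claimed for that case.

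**5. Sensitivity to baseline adjustment.** If the SD behind 264 is unadjusted and the baseline-to-follow-up correlation is 0.5 (an assumption), adjustment multiplies the variance by 1 − 0.5² = 0.75. At DE = 1.18 power is then about 84%. This restores power; it does not repair a standard error that ignores blocks.

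**The case against.** A reader might infer that every planned model treats participants as individually randomised. The article does not show that. The primary analysis is a mixed model with unstated random effects, which could include hospital or block, and the joint model contains the same mixed model. This is a condensed article, and a fuller plan may set out the random effects. What can be said is narrower: no model names such a term, and the ordinal, binary logistic and Cox models are named in plain form.

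A reader might also infer that 80% power and 5% error are certainly not delivered. That depends on an ICC that the article does not give. At the low end of the assumed range the figures are 79% and 5.2%, close to nominal, and nothing in the article supports 0.10 in particular. Without an SD, 264 cannot be proved free of a design effect either; the text simply describes none.

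Two further points stand. Each hospital cycles through the arms, so differences between hospitals largely cancel. Leaving site out of the model would by itself make the test conservative, so the net type I error of a model ignoring both site and block is not established by the block calculation alone. Baseline adjustment may also recover some or all of the lost power.

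None of this removes the mismatch between the unit of allocation and the stated basis for the sample size. The article discloses the block design but discusses only bias and contamination, not precision.

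**Conclusion.** The point holds in a limited form. Allocation is by hospital-by-period block. The 0.80 power for 264 describes no allowance for that, and no listed model names site or block. The direction of the effect is certain for any positive within-block correlation; the size is not. On the planned schedule, with an assumed ICC of 0.02–0.10, equal blocks and a back-solved SD of 2.35, power at 264 evaluable is about 79%–73% and the type I error of an analysis ignoring blocks about 5.2%–7.2%. The loss is materially larger only if blocks are fewer, larger or markedly uneven. The evidence does not support saying that the trial is badly underpowered or that the primary model is wrong. It supports saying that the power statement is unqualified where it needs qualifying, and that an analysis following the text as written could report intervals that are too narrow. This should be fixed.

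**What to change.** 1. Describe the allocation as a cluster-randomised crossover by time block within hospital.
2. In the linear mixed and joint models, include site as a fixed effect and a random intercept for site-by-block.
3. In the ordinal logistic, binary logistic and Cox models, include site, and account for block by block-clustered variance or, for the Cox model, a shared frailty.
4. Replace the unqualified 0.80 with the power for 320 enrolled over a stated ICC range. Give the SD, whether it is adjusted for baseline, the expected number and size of blocks, and the meaning of the three-group comparison for alpha.

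No extra enrolment or procedures are needed. Each participant's hospital and recruitment block must be available in the analysis data set; both follow from how arms are assigned. The cost is a slightly less favourable stated power and slightly wider intervals.

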**Methods and analysis:**

This is a three-armed randomised controlled trial, with two intervention groups (comprehensive and simple exercise programme) and a control group receiving usual care. We will include 320 participants aged ≥75 years from geriatric medical departments of four hospitals in Stockholm, Sweden. Assessments will be conducted at hospital admission, discharge and 3 months thereafter concerning physical function (primary outcome), activities of daily living, health-related quality of life, sarcopenia and falls. The number of readmissions will be registered up to 1 year after discharge. Data will be analysed with linear mixed effects models, according to the intention-to-treat approach.

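### With 320 enrolled and 20% loss, 256 participants have a 3-month SPPB, 8 fewer than the 264 the power statement needs (minor effect on power)

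*Protocol article*

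**What the plan says.** The sample size is set under Power of the trial in the protocol article. The base requirement is "We estimate that 264 participants should be included in the main RCT". The target is a "clinically meaningful difference of one point in the main outcome (SPPB) at 3 months after discharge", with power 0.80 and alpha 0.05 for a comparison of three groups.

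The allowance for loss follows: "To take into account, approximately 20%of deaths or dropouts during 3 months, 320 participants should be included in the trial". The Methods and analysis paragraph of the abstract repeats the enrolment figure: "We will include 320 participants aged ≥75 years".

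No other section gives a different loss rate, and the article does not show how 264 was turned into 320.

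**The concern.** The loss rate and the power claim refer to the same endpoint. The power is claimed for SPPB at 3 months, and the allowance covers people who die or drop out over 3 months. The enrolment figure should therefore leave 264 people after the stated loss, and it does not.

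What is at stake is whether the 80% can be repeated as it stands. A reader who applies the plan's own loss rate to its own enrolment figure gets fewer than 264 people and slightly less than 80% power. If the sentence is carried unchanged into the results paper, it will claim a little more than the design delivers.

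**Working it through.** **Inputs (all from Power of the trial):** required number 264; loss about 20%; enrolment 320; difference 1 SPPB point; power 0.80; alpha 0.05.

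**Reproducing the plan's 320**
- Adding 20% to the required number: 264 × 1.20 = 316.8, so 317, or 318 if rounded within three arms of 88 (88 × 1.20 = 105.6, so 106; 3 × 106 = 318). Rounding up again gives 320.
- Taking 20% from those enrolled: 264 / (1 − 0.20) = 330, or 110 in each of three equal arms. This does not give 320.

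The first form comes close to the printed figure and the second does not. Multiplying by 1.20 protects against a loss of 1 − 1/1.20 = 16.7% of those enrolled, not 20%.

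**What 320 delivers**
- At 20% loss: 320 × 0.80 = 256, and 264 − 256 = 8 short.
- Largest loss that still leaves 264: 1 − 264/320 = 17.5%.

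| Loss | Remaining of 320 | Enrolment needed to keep 264 |
|---|---|---|
| 15% | 272.0 | 311 |
| 17.5% | 264.0 | 320 |
| 20% | 256.0 | 330 |
| 22% | 249.6 | 339 |

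**Effect on power**

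The article prints no SD, sidedness or allocation ratio. I assume equal arms (88 per arm at 264; 256/3 = 85.33 per arm at 256) and take the SD that makes 264 give exactly 80%.

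*Pairwise, two-sided 0.05, normal approximation.*
- Implied SD = √(88/2) / (1.960 + 0.842) = 6.633 / 2.802 = 2.37.
- At 85.33 per arm: √(85.33/2) / 2.368 − 1.960 = 2.759 − 1.960 = 0.799, so power is 78.8%.

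*Pairwise, Bonferroni 0.05/3.*
- Implied SD = 6.633 / (2.394 + 0.842) = 2.05.
- At 85.33 per arm: 6.532 / 2.050 − 2.394 = 0.792, so power is 78.6%.

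*Three-group F-test at 0.05.*
- With group means 0, 0, 1 the implied SD is 2.45. With means 0, 0.5, 1 it is 2.12.
- At 256 in total, both patterns give 78.7%.

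The implied SD changes with the test, but the fall in power hardly does. It is 1.2 to 1.4 percentage points in every case.

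**The case against.** There are three fair points on the other side.

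1. **The rate is approximate.** The plan writes "approximately 20%of deaths or dropouts during 3 months", and a forecast of 17.5% could be rounded to that. This narrows the point but does not remove it. The same wording would cover 22%, which leaves about 250. If 17.5% was the planning figure, the sentence should say so.

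2. **People without a 3-month measurement are not wholly lost.** The analysis is by intention to treat, with mixed models and joint models for death and loss to follow-up. SPPB is also measured at discharge (Table 2), so someone lost after discharge still contributes. The number 256 is therefore the count with a 3-month SPPB, not the analysed sample. Some information is recovered, but the article gives nothing from which to size it. The power statement does not rely on it either: it is framed at 3 months and makes its own allowance for loss.

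3. **The effect is small.** This stands in full. It limits the weight of the point, not its correctness.

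A reader might also infer that the authors are known to have multiplied by 1.20 instead of dividing by 0.80. The closeness of 316.8 to 320 suggests it, but without a printed formula it remains an inference. The mismatch between 264, 20% and 320 is there whatever its cause.

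**Conclusion.** The point holds as a minor arithmetic inconsistency. At the stated loss rate, 320 enrolled leaves 256 with a 3-month SPPB, against 264 required. The enrolment that matches 20% loss is 330, and the loss that matches 320 is 17.5%. That part uses printed figures only.

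The power figure of about 78.6% to 78.8% rests on equal arms, on 264 giving exactly 80%, and on an SD back-solved from that. It also counts only participants with a 3-month measurement.

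A reader might infer that the trial is materially underpowered, particularly as groups are recruited in time blocks. The loss arithmetic does not support that: it costs less than 1.5 percentage points. Any effect of clustering by block is a separate question. The article gives no intracluster correlation, so a clustering figure would rest on an outside assumption and does not belong to this point.

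**What to change.** Correct the sentence under Power of the trial in one of two ways:

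- keep 320 and say that it retains the required 264 only if loss by 3 months is at most 17.5%; or
- keep the 20% loss and say that 320 enrolled leaves 256 with a 3-month SPPB and power of about 79%, naming the comparison and assumptions behind that figure.

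The cost is one sentence with a slightly less favourable number. Enrolment, design and analysis stay as they are. The Trial status section already commits the authors to posting deviations from the protocol on the registry and reporting changes with the results, so the correction can follow that route.

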This trial has some limitations. First, instead of a classic randomisation, we have chosen a block design, which may introduce selection bias in the trial. However, an advantage of the block design is that it avoids copresence of participants from both groups at the same department; and thus, prevents that the exercises in the intervention groups will spread to ordinary treatment and risk to contaminate the control group. If the exercises in the intervention groups would spread to the control group and produce unexpected clinical benefits, it could create a bias by disguising a possible genuine benefit of the interventions and reduce the effect size to a value that is not clinically significant. Therefore, it has been emphasised that researchers in clinical trials on rehabilitation topics should make sure that control groups do not include any of the active elements of the intervention such as physical exercise.^12^ Second, like usual care in the studies by Martínez-Velilla *et al* and Ortiz-Alonso *et al*,^10 11^ usual care at geriatric departments in Sweden include physiotherapy, and the patients may receive a limited amount of functional training when needed. This may introduce a bias in the trial since participants in the control group may also receive some physical exercise. However, a hospital stay is often accompanied by low levels of physical activity, which has been suggested to play a major role in causing the negative health consequences associated with hospitalisation.^4 14^ Third, the trial will include participants who are able to stand up from a sitting position, and to communicate and collaborate with the research team, which could limit the generalisability to those with relatively higher levels of functioning. However, the trial participants will be consecutively recruited at several hospitals, so that the sample will be representative of older hospitalised patients.

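### The stated adjustment for SPPB and the other continuous outcomes is the baseline score alone, although the article concedes possible selection bias and already collects frailty, comorbidity and other prognostic data

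*Protocol article*

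**What the plan says.** All references are to the protocol article.

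- **Continuous outcomes** (Data analysis, text under Power of the trial). Between-group comparisons of change "will be conducted using linear mixed effects models, with adjustments for baseline scores". No other adjustment is named for these models.
- **Joint models** (same place). Their stated purpose is different: "To account for deaths and lost to follow-up, we will model the group comparisons through joint models". They deal with who leaves the trial, not with who entered each arm.
- **Sex** (same place). It appears only as an effect modifier: "Multiplicative interactions between sex and group allocation in relation to the outcomes will also be examined".
- **Other outcomes** (same place). Only model types are given. Readmissions get an ordinal logistic model and deaths a Cox model; for the remaining type the text reads: "Binary logistic regression models will be employed to examine between group differences in binary outcomes". No covariates are mentioned for any of the three, either to include or to exclude them.
- **Allocation** (Trial design). Each site recruits to one group at a time in blocks of 2–3 weeks, with the order of groups randomised per site.
- **Conceded risk** (Discussion, and the strengths and limitations box). In the Discussion: "we have chosen a block design, which may introduce selection bias in the trial". The counterweight offered is avoidance of contamination.
- **Baseline data** (Data collection). Age, sex and cohabitation status are collected, together with "reason for hospital admission, comorbidities, frailty status and nutritional risk". Frailty is graded on the Clinical Frailty Scale and nutritional risk on the Mini Nutritional Assessment-Short Form.

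**The concern.** Under concealed individual randomisation, covariate adjustment is mainly a matter of precision. Here it also bears on bias. A department is on one arm for weeks at a time, so it is plausible that people involved in recruitment come to know the current arm. The eligibility criteria leave room for judgement: the responsible physician may exclude patients with a major condition that contraindicates exercise. That judgement could fall differently in exercise and control blocks, and it would act on frailty and comorbidity.

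Two patients with the same SPPB during acute illness, one robust before admission and one frail, need not recover alike. If the arms differ in the mix of such patients, adjusting for baseline SPPB leaves part of the difference in the 3-month comparison, where it would be read as an effect of exercise. The variables that could reduce this are collected, but the main comparison gives them no role. The Discussion mentions frailty level only for later post hoc work on who benefits from the intervention.

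**Working it through.** **Does the plan's own figure bear on this?** The target is one SPPB point at 3 months with 264 participants (88 per arm), power 0.80 and alpha 0.05. No standard deviation (SD) is given, so 264 cannot be reproduced. Solving backwards for a two-sided pairwise comparison:

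SD = √(88/2) / (1.960 + 0.842) = 6.633 / 2.802 ≈ 2.37.

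With alpha 0.05/3 the implied SD is about 2.05. I use SD 2.36, which returns 88 per arm after rounding up. It serves only as a scale for the standard error and is an assumption.

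**Residual bias in SPPB, no true effect.** Let b be the effect of an omitted binary factor on 3-month SPPB among patients with equal baseline SPPB, and d the difference in its prevalence between arms. Both are assumed.

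- Bias = b × d.
- Standard error = 2.36 × √(2/88) = 0.356.
- Two-sided type I error = 1 − [Φ(1.96 − bias/SE) − Φ(−1.96 − bias/SE)].

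| b (points) | d = 0.05 | d = 0.10 | d = 0.15 |
|---|---|---|---|
| 0.5 | 0.025 (5.1%) | 0.05 (5.2%) | 0.075 (5.5%) |
| 1.0 | 0.05 (5.2%) | 0.10 (5.9%) | 0.15 (7.1%) |
| 2.0 | 0.10 (5.9%) | 0.20 (8.7%) | 0.30 (13.5%) |

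Cells show bias in SPPB points, with type I error in brackets. The bias does not depend on the SD. The type I error does, and a smaller SD would raise it.

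**How much does baseline SPPB already remove?** A simulation (2,000 runs, 88 per arm, no true effect) assumed that half of patients above Clinical Frailty Scale 6 were kept out of exercise blocks but not control blocks. The mean frailty difference was then about 0.18 levels. The spurious SPPB difference was 0.18 points unadjusted, 0.07 with baseline SPPB, and 0.00 with frailty added. Baseline SPPB thus removed (0.18 − 0.07)/0.18 ≈ 61%. The final zero is built in, because selection was simulated on frailty alone.

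**Precision.** In that simulation the standard error fell from 0.296 to 0.288. The variance ratio is 0.288²/0.296² = 0.947, a reduction of about 5%. At 5%, the gain is 264/0.95 − 264 ≈ 14 participants.

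**Binary outcomes, if analysed without covariates.** Assume a 20% event rate, 107 per arm (320/3), and an omitted factor with 50% prevalence and odds ratio 2–3. With an imbalance of 5–15 percentage points and no true effect, the crude odds ratio is 0.97–0.86 instead of 1.00, and the type I error is 5.1%–7.4%.

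Both type I error calculations use a normal approximation and treat patients as independent.

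**The case against.** The strongest counter-argument has four parts.

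1. **The secondary models.** A reader might infer that the readmission, binary and mortality models will be unadjusted, so that nothing protects them. The text does not support this. It names model types and is silent on covariates. In a condensed article with no analysis plan shown, such lists may well sit elsewhere. This part of the objection stands: silence is not a decision, and those models enter here only as a place to carry the same set over.

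2. **The size.** A reader might also infer that any selection bias goes straight into the SPPB result. It does not. The article says only that bias may arise, and baseline SPPB removed about 61% in the scenario above. The remaining 0.07 points is 7% of the target difference; 0.07/0.296 = 0.24 standard errors gives a type I error of about 5.6%. This stands too.

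3. **The assumptions.** The documents give no frailty distribution and no imbalance. Eligibility narrows the frail end in every arm: patients must be able to stand with at most minimal help, and nursing-home residents and the terminally ill are excluded. Recruitment is consecutive, block order is randomised and assessors are blinded. That recruiters know the current block is an inference, not something the article states. All of this limits how confidently a size can be given.

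4. **The remedy.** Covariates correct only measured and properly modelled imbalance. This is true and should be stated in the plan.

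One thing remains. For the continuous outcomes, including the primary one, the article does state an adjustment set. That set leaves out every prognostic factor other than the baseline score, in a design whose selection risk the article itself concedes.

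**Conclusion.** The point holds for SPPB and the other continuous outcomes. The stated adjustment is the baseline score only, no analytic response to the conceded selection risk is given, and a better-specified model is available from data already collected. It is an improvement worth making, not an error that invalidates the analysis.

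The size cannot be derived from the documents. Under the assumed inputs the residual bias is roughly 0.03–0.30 SPPB points, with type I error between 5.1% and 13.5%; the upper end needs a strong factor and a 15-point imbalance together. The simulated precision gain is small, worth about 14 participants. For readmissions, binary outcomes and mortality, the supportable statement is only that the article names no covariates.

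**What to change.** In the Data analysis text, before outcomes are examined by group:

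- State that the linear mixed and joint models for SPPB and the other continuous outcomes include age, sex, Clinical Frailty Scale, nutritional risk, number of comorbidities and site, in addition to the baseline score. Site belongs in the set because block order is randomised within site. With four hospitals this adds 5 + 3 = 8 parameters if each patient factor takes one term, which 264 participants can carry.
- Make this the main estimate and keep the baseline-score-only estimate as a sensitivity analysis.
- Apply the same prognostic set to the readmission, binary and mortality models, shortened in advance if events are few. Add baseline sarcopenia status to the sarcopenia model; Table 2 shows that it is measured.
- Say how missing covariates are handled.
- State that adjustment reduces bias from measured factors only, and that unmeasured selection and calendar-time effects remain.

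The cost is slightly more analysis work, the handling of missing covariates, and odds and hazard ratios that become conditional on the covariates. No new data are needed. The article describes version 1 of the protocol with recruitment ongoing and provides for updating changes on the trial registry. Fixing the set now also prevents covariates from being chosen after an imbalance is seen.
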